## 3. Discussion

The development of this study could facilitate the creation of future clinical guidelines on the use of physical therapy through telerehabilitation platforms in the public health field.

The need to treat these patients in the short, medium and long term after discharge from hospital is an unavoidable commitment for the society that must assess the socio-economic impact and persevere in the search for effective interventions. This situation of world crisis is presented as an opportunity to continue developing professionally and scientifically, to implement the advantages offered by new technologies in the field of telerehabilitation, as well as to seek opportunities to solve the possible shortcomings of the Health Systems.

The current questions about the effects caused by COVID-19 should not limit us to act—on the contrary, it should stimulate the search for solutions that can bring pulmonary rehabilitation closer to patients who need it after discharge from hospital. In this sense, telerehabilitation is seen as a tool that could provide an efficient and cost-effective response to the health problems identified [12]. Physiotherapy will play a fundamental role, not only in the intensive care units and in the hospitalized patients, but it will also be a cornerstone in the interdisciplinary health team for the recovery of the sequelae which should lead to an improvement in the quality of life of patients with COVID-19 [12].

Telemedicine has the promise of improving quality, increasing patient access and reducing health care costs [44]. Studies have shown that telerehabilitation is effective in improving clinical outcomes in various pathologies suggesting that the increased intensity provided by telerehabilitation is a promising option to be offered to patients [27]. Recent research concludes that telerehabilitation appears to be a viable option for selected hospitalized patients with COVID-19 and may be a safe way of delivering inpatient rehabilitation to isolated or at-risk populations [45]. Although a recent systematic review indicates that telerehabilitation may be safe and feasible and may lead to reduced face-to-face rehabilitation therapy; in addition, remote rehabilitation assessment should be considered during the COVID-19 pandemic [46]. Another important fact is that the reported number of adverse events was low, and most studies reported that the average session adherence rate was >70% [46].

Unlike other studies that require software implementations in specific devices, our intervention generates few obstacles since it is available in any device that allows internet connection and that patients usually have (personal computer, laptop, tablet, smartphone) allowing access from any location and different devices. This contrasts with other studies that require a highly complex technological platform, software installation and multidirectional cameras for controlled clinical control connecting the healthcare provider and the patient [47]. As the patient uses his own technological devices, the rapid implementation process is guaranteed. This, however, may lead to a selection bias for those patients without access to technology. Technical problems (disconnection, device failures) and technological difficulties may arise in connection with the use of technology. However, staff members will be available to provide technical support to patients by phone or email, without the need to visit the patient at home to install or check any hardware.

The lack of improvement and positive evolution of the patient, as well as the appearance of a low level of adherence was considered as possible adverse events. Also is considered as an adverse event, the performance of movements with excessive workload that cause muscle overload.

Patients will be informed of the importance of warning the healthcare professional of any incident or setback in their recovery, as well as their right to withdraw from participation in the research at any time.

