The main objective of this research is to evaluate the effectiveness of a personalized telerehabilitation intervention in patients diagnosed with COVID-19 after discharge from hospital for the improvement of functional capacity and quality of life compared to a program of health education and/or care in a rehabilitation center. As secondary objectives, to identify the satisfaction and perception of patients with the telerehabilitation intervention and the presence of barriers to its implementation, as well as to evaluate the cost-effectiveness from the perspective of the health system. The hypothesis of this research is that the implementation of a telerehabilitation (TR) program in patients with COVID-19 presents no inferior results in the improvement of functional capacity and quality of life compared to those obtained with a health education program and/or care in a rehabilitation center.

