### 2.3. Intervention

The TR group receives a personalized program for 8 weeks, including at least one session per day and is done through a web and mobile application. The telerehabilitation application allows health professionals to create personalized exercise programs, hold video conferences with patients, generate videos, images and parameters of each exercise, as well as send them by email and follow up patients through the mobile application.

The TR program describes the exercises to be performed, the number of series and repetitions, and the criteria for progression, which will be based on the clinical guidelines published for patients with COVID-19 and described in the introduction section. The Physiotec software was selected by the research team to be best suited to the needs of the patients.

Patients are initially supervised by the research team who will conduct training sessions to ensure proper execution of the exercises and encourage patient adherence. Patients will be instructed to perform self-training by following the video exercises through the TR program, as well as a support document called COVID-19 Patient Telerehabilitation Manual. The number of synchronous sessions (1 to 1) via videoconference will be determined by the initial evaluation, limiting the interventions to 1 session per day of maximum 45–50 min, always adapted to the previous evaluation and to the needs of each patient.

Patients will be advised to refrain from any other specific training during the intervention period. Any deviation from the adherence and practice of the TR program is recorded on a daily basis, noting any adverse incidents.

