Telerehabilitation and physical therapy interventions may include aerobic training—generate exercise patterns such as walking, fast walking, jogging, swimming, etc., starting at a low intensity and duration and increasing gradually; 20–30 min of session duration is recommended, 3–5 sessions/week, although it will always depend on the sensation of fatigue and/or dyspnea that each patient presents [18]. Progressive strength training is recommended working 1–3 muscle groups with a load of 8–12 repetitions, with 2-min training intervals. The frequency would be 2–3 sessions/week for a minimum period of 6 weeks, increasing the load by 5–10%/week [18]. Secretion drainage or ventilatory techniques to re-educate the respiratory pattern, improve ventilation, mobilize the thorax and favor secretion drainage, especially in those patients with chronic pathology prior to COVID-19 or who have a reduced pulmonary capacity to cause the disease [36].

Due to the lack of detailed knowledge of sequelae, a correct evaluation of each particular case is recommended before applying physiotherapeutic techniques [16]. The software and the mobile application for such intervention are provided and financed by exclusive license by the principal researcher. Customized exercise program examples are available at main author request.

The control group (CG) receives the standard of care recommended for patients discharged from hospital. Based on the individual needs of each subject, it consists of a rehabilitation program in their hospital or primary care center of reference, in the event that they present evidence of immunity and the evaluation of the sequelae requires it. If you do not present proof of immunity or if you test positive for COVID-19, you will receive a recommendation for confinement for a minimum of 14 days and a health education program to be carried out at home where recommendations for the care of health sequelae are included.

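### The adverse event definition takes in lack of improvement and low adherence, and active daily noting is described only for the TR programme, so an adverse event tally would partly restate efficacy and adherence

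*Protocol article*

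**What the plan says.** The definition stands in section 3 (Discussion) of the protocol article. It begins with "The lack of improvement and positive evolution of the patient" and continues "as well as the appearance of a low level of adherence was considered as possible adverse events". The next sentence adds "the performance of movements with excessive workload that cause muscle overload". These three items are all that the article names as adverse events.

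On recording, section 2.3 (Intervention) says, within the description of the TR arm: "Any deviation from the adherence and practice of the TR program is recorded on a daily basis, noting any adverse incidents". The control arm's paragraph in the same section opens with "The control group (CG) receives the standard of care recommended for patients discharged from hospital" and goes on to describe the care given; it mentions no log. The Discussion adds a route that is not limited to one arm: "Patients will be informed of the importance of warning the healthcare professional of any incident or setback in their recovery".

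The hypothesis, at the end of section 1.2, is that TR "presents no inferior results in the improvement of functional capacity and quality of life" compared with the control programme.

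**The concern.** An adverse event count should measure harm. Two of the three named items do not. Lack of improvement is the efficacy result seen from the other side, so a patient who does not improve is counted once as an efficacy failure and again as a possible adverse event. Low adherence describes how the programme was taken up. Only the item on overload points to an injury.

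The article hopes to inform guidelines and policy on telerehabilitation after hospital discharge, and TR patients do part of their exercise by self-training from videos. A reader will want to know whether this caused harm. On the stated definition the count moves with efficacy: if TR works better it looks safer, and if it works worse it looks less safe, even when injuries are equal. Noting incidents more actively in one arm than in the other adds a second reason for counts to differ without a difference in harm.

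**Working it through.** The plan states no adverse event rate, safety hypothesis or safety sample size, so there is no figure to reproduce. The check is first of the text, then an illustration on assumed rates.

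**Text, side by side**

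| Item named in the Discussion | What it measures | Where else the trial captures it |
|---|---|---|
| Lack of improvement | Efficacy | STS, SPPB, SF-12 and EQ-5D in both arms at T.1 and T.2 (section 2.5, Table 1) |
| Low adherence | Process | Daily TR deviation record (section 2.3); number of sessions in both groups for direct costs (section 2.4.3) |
| Overload from excessive workload | Harm | Daily TR record of incidents (section 2.3); self-report by patients (Discussion) |

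The first two items are thus already captured elsewhere, at least in part. Counting them as adverse events adds no safety information.

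**Illustration 1: effect of the definition**

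Assumptions, none from the documents: true harm h = 5% in each arm; non-improvement n_C = 30% in control and n_T = 20% or 40% in TR; harm and non-improvement independent; low adherence left out.

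Proportion counted with an event = 1 − (1 − h)(1 − n).

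- Control: 1 − 0.95 × 0.70 = 33.5%.
- TR, n_T = 20%: 1 − 0.95 × 0.80 = 24.0%.
- TR, n_T = 40%: 1 − 0.95 × 0.60 = 43.0%.

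Share of counted control patients who are non-improvers only = (1 − h) × n_C ÷ 0.335 = 0.95 × 0.30 ÷ 0.335 = 85%.

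With h = 10% the control figure is 1 − 0.90 × 0.70 = 37%, and the share is 0.90 × 0.30 ÷ 0.37 = 73%.

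True harm is identical in every case. TR appears safer or less safe only because efficacy differs.

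**Illustration 2: effect of unequal capture**

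Assume equal true risk, full capture in TR and a fraction a captured in control. The apparent risk ratio is 1/a: 1.33 for a = 0.75, 2.0 for a = 0.50 and 4.0 for a = 0.25. The documents do not say what a is. It could be close to 1 if the full protocol collects events in the same way in both arms.

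**The case against.** The strongest reply is that no safety comparison exists to be biased. The objectives, the outcome measures (section 2.4), the statistical analysis (section 2.5) and Table 1 contain none; the planned group comparisons are of means. This stands, and it makes the consequence conditional.

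The second reply is that a condensed article need not describe control-arm event collection or show a safety row in its schedule. This largely stands too. The silence does not show that the full protocol lacks either, and no finding is made of the missing row.

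The third is that no pooling rule is stated, so events could be listed by type, which would keep overload visible. That is possible, but the definition would still label non-response and non-adherence as adverse events.

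Three stronger readings are tempting and not supported:

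- A reader might infer that TR is charged with events that control patients cannot have. The Discussion speaks of the patient without naming an arm. Control patients can fail to improve, and those in a rehabilitation programme or following home advice can adhere poorly or overload a muscle.
- A reader might infer that harm in control goes unnoticed. The request to report incidents and setbacks is not limited to TR. It is a passive route, so control events may be sought less actively, but they are not shut out.
- A reader might try to count TR patients with low adherence from the average session adherence above 70% that the Discussion cites from other studies. That is a mean over sessions, not a share of patients, and the article gives no threshold for low adherence. No count follows.

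None of this answers the first half of the point. The definition is stated, so it is not a detail left to another document.

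**Conclusion.** The point holds in a limited form. As written, the definition mixes the efficacy outcome and a process measure with harm, and active daily noting of incidents is described only for the TR programme, against passive self-report for patients in general. Any tally on this basis would partly restate efficacy and adherence, and a between-arm comparison of it would be hard to interpret.

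The definition half rests on the text alone. The recording half is weaker, because it rests on what a condensed article describes. The size cannot be derived from the documents: the 85% (or 73%) share and the risk ratios of 1.33 to 4.0 show direction and possible scale under assumed rates, and are not estimates for this trial. The efficacy analyses do not use the adverse event count and are untouched. The correction is worth making because it is cheap and because safety will be asked about when the results are reported.

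**What to change.** 1. In the Discussion, define an adverse event as any untoward medical occurrence after randomisation, in either arm, whatever its cause.
2. Take lack of improvement out of the definition and report it only as efficacy. Take low adherence out and report it as a separate process measure.
3. Ask the same adverse event question in both arms at the existing T.1 and T.2 assessments, and base any between-arm summary on that source. Since the evaluator is blind to allocation, ask it after the outcome tests or on a form the patient completes.
4. Keep the TR daily log and list its events separately, outside any between-arm summary.

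The cost is a change of wording and a few minutes at each of two existing visits. Neither the sample size nor the efficacy analysis changes.

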## 4. Conclusions

This research should provide knowledge about the possibility of implementing TR programs in patients with COVID-19 after discharge from hospital, identifying health resources and allocated costs that will allow the definition of new intervention policies in this group of patients.

## Figures and Tables

**Figure 1 ijerph-18-02924-f001:**
[figure not shown]
Study design.

**Figure 2 ijerph-18-02924-f002:**
[figure not shown]
Short performance physical battery test (SPPB) based on Riskowski JL et al.

**Table 1 ijerph-18-02924-t001:** Schedule of enrolment, interventions, and assessments.

	Enrolment	Allocation	Post Allocation		Close out
Time Point	−T 1	T 0 [Baseline]	T.1 [4 Weeks]	T.2 [8 Weeks]	
ENROLMENT:					
Eligibility screen	X				
Informed consent	X				
Advance info	X				
Allocation		X			
INTERVENTION:					
TR Group					
Control Group					
ASSESMENT:					
Baseline Variables	X				
Initial Assesment		X			
STS Test		X	X	X	X
SPPB test.		X	X	X	X
SF-12 and EQ-5D		X	X	X	X
TSUQ			X	X	X
Direct Costs			X	X	X
Data Collection					
Statistical Análisis					X

## Data Availability

The Researcher declares that he follows the protocols of his work centre regarding the publication of data in accordance with the provisions of Organic Law 15/1999, of 13 December, on the Protection of Personal Data (LOPD), and that the data will be incorporated into a file for the purpose of carrying out this research project. Participating subjects will be informed of the possibility of exercising their rights of access, rectification, cancellation and opposition of their data at the e-mail address provided by the principal investigator.

## Abbreviations

SARS-CoV-2: Severe Acute Respiratory Syndrome Coronavirus. COVID19: Coronavirus Disease 2019. TR: Telerehabilitation. SQUIRE: Standards for Quality Improvement and Excellence in Reporting. SPIRIT: Standard Protocol Items Recommendations for Interventional Trials. IC: confidence index. CG: Control Group. STS: sit-to-stand test in 1 min. 6MWT: 6-min walk test. SPPB: short performance physical battery test. SF-12: Short Form Health Survey 12. EuroQoL-5d: European Quality of Life-5 Dimensions survey. SF-36: Short Form Health Survey 36, VAS: visual analogue scale. TSUQ: Telemedicine Satisfaction and Usefulness Questionnaire. CONSORT: Consolidated Standards of Reporting Trials
